##### Cervical JPE

Cervical JPE will be measured using a laser-pointer attached to a lightweight headband as described by Revel et al. [13]. Participants will be seated 90 cm away from the target. They will be blindfolded and asked to perform an active movement (extension and rotation to the left and right) and return to the starting head position as accurately as possible. An absolute error between the starting and end points will be calculated in millimeters and then converted to degrees. Three repetitions of each movement direction will be undertaken and the mean value of the error will be used for analysis. This method has been shown to have good test-retest reliability (ICCs = 0.73-0.84) and high validity (r with three-dimensional ultrasound based technique = 0.95) [41].

#### Secondary outcomes

*Gait speed:* Participants will be instructed to walk barefoot over 10 m at a comfortable speed and then with head turns from side to side. The time will be measured for the intermediate 6 m to exclude acceleration and deceleration [42]. Each test will be performed twice with a 60-s rest period and the mean value used in analysis. Gait speed has been shown to be a reliable measure of functional capacity (ICC for test-retest reliability = 0.90) [43].

##### Dizziness intensity

Intensity of dizziness will be measured using a VAS [22]. Participants will be asked to indicate their average dizziness intensity over the past week by marking a horizontal 100 mm line (0 = no dizziness and 100 = worst dizziness imaginable).

##### Neck pain intensity

Neck pain intensity will be measured using a VAS. Participant will be instructed to grade their average intensity of neck pain experienced in the past week on a 0-100 mm horizontal line (0 mm = no pain and 100 mm = worst pain imaginable) [44]. The VAS has been shown to have excellent test-retest reliability (ICC = 0.97) and high validity (r with a 5-point verbal descriptive scale = 0.71-0.78) to evaluate pain perception [45, 46].

##### Neck disability

Neck disability associated with neck pain in the past week will also be measured using the NDI-TH [47]. The NDI-TH has a total of 10 sections concerning pain and activities of daily living, with a maximum score of 50. A higher score indicates greater disability. The NDI has been shown to have high validity (r with the McGill pain questionnaire = 0.69-0.70) and excellent test-retest reliability (ICC = 0.89) [48].

##### Pain extent and location

Pain drawings will be used to assess the participants’ extent and location of pain, using a digital device (iPad Air 2) and custom software [49]. Participants will be instructed to draw their pain perceived during the last week using a stylus pen on body charts with different views (frontal, dorsal, lateral right and left). They will also be asked to nominate and mark the most painful site. The type, size and colour of the pen strokes will be standardized across all participants. Custom software will be used to quantify pain extent and location. This pain drawing acquisition and analysis has been shown to be a reliable tool to evaluate the location and extent of pain in neck pain (ICC for test-retest reliability = 0.92) [49, 50].

##### Cervical range of motion

A cervical range of motion (CROM) goniometer (Performance Attainment Associates, USA) will be used to assess cervical range of motion in flexion, extension, left-right lateral flexion and left-right rotation. Participants will be seated upright and asked to actively move their neck in each direction three times. Any pain or dizziness provoked will be recorded on a 0-10 NRS. The CROM has been shown to have excellent test-retest reliability (ICCs = 0.89-0.98) and high validity (r with Fastrak motion analysis system = 0.93-0.98) [51].

##### Functional ability status

The patient-specific functional scale (PSFS) will be used to assess participants’ functional status [52]. Participants will be asked to nominate 3 to 5 activities that they are unable to do or having difficulty doing because of their neck pain. These activities will be rated on a 0-10 scale, where 0 is unable to perform the activity and 10 is able to perform the activity at same. An average of all activities scores will be used for analysis. The PSFS has been shown to have high validity (r with NDI = 0.73-0.83) and excellent test-retest reliability (ICC = 0.92) [52].

##### Health-related quality of life

The Thai version of Short Form-36 will be used to assess participants’ health-related quality of life. The instrument has been shown to have moderate to good internal consistency reliability (Cronbach’s α = 0.55-0.80) and good discriminant validity for use in a general population [53]. It contains 36 questions, divided into 8 dimensions of quality of life. These include physical functioning (10 items), role limitations due to physical health problems (4 items), social functioning (2 items), bodily pain (2 items), general mental health (5 items), vitality (4 items), role limitations due to emotional health (3 items), general health perceptions (5 items) and reported health transition (1 item). The scores for each question will be the weighted sum of the questions in each dimension. Scores range from 0 to 100, with a higher score indicating better health status.

##### Global perceived benefit of treatment

A seven-point ordinal Likert scale will be used to allow the participant to express how much they perceived a benefit from the treatment. The scale ranges from 1 (extremely dissatisfied) to 7 (extremely satisfied) [54].

### Randomization and allocation concealment

All eligible participants will be randomly allocated to one of four intervention groups: i) local neck treatment, ii) local treatment plus sensorimotor control exercises, iii) local treatment plus balance exercises, or iv) local treatment plus sensorimotor control and balance exercises. Randomization will be undertaken by an independent person with no other involvement in the trial. Random sequence will be generated by a computer permuted blocks of eight, stratified by age (≤ or > 45 years old) and dizziness (yes or no), with allocation ratio 1:1:1:1. Allocation will be concealed in sequentially numbered, sealed, opaque envelopes.

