### Study hypotheses

Primary hypothesis: Specific training of impairments in sensorimotor control and balance will be superior for improving impairments in neck proprioception and balance.

Secondary hypothesis: Specific training of impairments in sensorimotor control and balance will be superior for reducing dizziness intensity and increasing gait speed. There will be no differences between intervention groups in outcomes of neck pain intensity, neck disability, pain extent and location, cervical range of motion, functional ability, treatment satisfaction and quality of life.

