For those provisionally eligible for the trial, appointments will be made with an experienced physiotherapist who will be blinded to participant group allocation if accepted for the trial. The experienced physiotherapist will perform a physical examination of the neck and test sensorimotor function and balance. The physical examination includes:*Tests of cervical joint position error (JPE)* [9, 13]*.* The task is to return to the starting position as accurately as possible with the blindfold. Three trials will be performed of right and left rotation and extension. An average absolute error of > 4.5° in any direction is indicative of a deficit in cervical joint position sense [34].*Tandem stand test* [35]. The participants stand heel to toe with the dominant foot behind the non-dominant foot on a firm surface with eyes closed (age ≤ 45 years) or with eyes open (age > 45 years) [36]. An inability to maintain the standing position without taking a step for 30 s indicates balance impairment [36].*Manual examination of the cervical spine.* The physiotherapist will palpate the cervical facet joints from C0-1 to C7-T1 bilaterally. A joint will be classified as symptomatic by a combination of pain provoked > 2/10 and the physiotherapist’s rating of at least moderately abnormal tissue resistance [37].

All participants will be provided information about the study and enrolled into the trial if they meet all eligibility criteria and voluntarily sign an informed consent statement.

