### Physiotherapist training and treatment fidelity

The interventions will be provided by five physiotherapists who are experienced in the trial interventions and who have at least 5 years clinical experience in musculoskeletal physiotherapy. Each physiotherapist will deliver all intervention arms. The physiotherapists will attend a 3 h training session to enhance standardization of the interventions. The physiotherapists will be randomly assigned to each participant using computerized random numbers. Training will be provided by an experienced musculoskeletal physiotherapist and trial physiotherapists will receive a detailed procedural and treatment manual. Participant case notes will be monitored as will be selected. Treatment sessions will be audited to ensure that the physiotherapists are managing patients as per the trial treatment protocols.

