### Statistical analysis

SPSS version 17.0 or higher will be used for statistical analysis. Descriptive statistics will be used to describe demographic data and baseline characteristics and follow-ups for each treatment group. Two-way mixed ANOVA will be used to determine within-subject and between subject variables. Main effects for independent variables (local treatment/sensorimotor exercise and local treatment/balance exercise) and the intervention effects of the independent variables immediately after treatment and at 3, 6 and 12 month follow-ups will be analyzed. This allows the individual effects of sensorimotor exercise and balance exercise to be examined as well as whether there will be an additive effect of applying both sensorimotor and balance exercises in a multimodal treatment. Differences in mean change (baseline minus follow-up) will be compared between groups using baseline values of the outcomes as covariates.

Effect sizes will be calculated by taking the difference in mean changes in the primary outcomes between the intervention groups and control group (local neck treatment alone). An effect size of 0.2 will be regarded as small, 0.5 as medium and 0.8 as large [55]. Main comparative analysis for primary and secondary outcomes will be performed using an intention-to-treat approach. To address missing data, multiple imputation will be performed as a sensitivity analysis. The significance level will be set at 0.05.

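### Randomisation is stratified by age and dizziness, but the stated group comparison adjusts only for the baseline outcome, so intervals will be slightly wider than the design warrants

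*Protocol article*

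**What the plan says.** Protocol article, Randomization and allocation concealment: the allocation list is "stratified by age (≤ or > 45 years old) and dizziness (yes or no), with allocation ratio 1:1:1:1". Two binary factors make four strata. The section also sets a block size of eight. Over four arms this puts two participants per arm in each complete block, so the arms are kept close to balanced within every stratum.

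Protocol article, Statistical analysis: "Two-way mixed ANOVA will be used to determine within-subject and between subject variables". The covariate set follows: "Differences in mean change (baseline minus follow-up) will be compared between groups using baseline values of the outcomes as covariates". The section then covers effect sizes, intention-to-treat and multiple imputation. It mentions age group, dizziness or stratum nowhere, either as covariates or as factors.

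**The concern.** A factor used to restrict randomisation is normally carried into the analysis. Stratified blocks stop between-stratum differences from adding to the sampling variation of the treatment contrast. If the model leaves the strata out, it does not know this. It counts between-stratum differences as error and reports a standard error larger than the true one.

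At stake is some reported precision on the primary outcomes (postural sway and joint position error) and on the secondary outcomes. The validity of the comparisons is not at stake.

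**Working it through.** The article gives no figure to reproduce here: it states neither the variance explained by the strata nor a covariate-adjusted power calculation. The size therefore has to be shown over an assumed range.

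**Inputs**
- From Sample size: 35 participants per group before the dropout allowance, so 4 × 35 = 140 analysed.
- From Randomization: four strata, blocks of eight, equal allocation.
- Assumed: R², the share of residual variance explained by the two strata once the baseline outcome is in the model.

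**Interval width.** With balanced strata, width without strata ÷ width with strata = 1/√(1 − R²). The equivalent sample size is 140/(1 − R²).

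| R² (assumed) | Width ratio | Excess width | Equivalent n |
|---|---|---|---|
| 0.01 | 1.005 | 0.5% | 141.4 |
| 0.05 | 1.026 | 2.6% | 147.4 |
| 0.10 | 1.054 | 5.4% | 155.6 |
| 0.20 | 1.118 | 11.8% | 175.0 |

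**Cost in degrees of freedom.** Intercept, two main effects, their interaction and the baseline outcome use five parameters, leaving 140 − 5 = 135. Two stratum terms leave 133. The change in the t quantile alters the width ratio only in the fourth decimal (at R² = 0.05, from 1.0260 to 1.0258).

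**Simulation check.** The 2 × 2 design was simulated with 140 participants, four strata, blocks of eight, no treatment effect, and 2,000 runs per setting. The assumed coefficient of follow-up on baseline within strata was 0.5. Both stratum factors shifted baseline and follow-up by the same amount.

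| Shift per factor (within-stratum SD) | Width ratio | Type I error, strata omitted |
|---|---|---|
| 0.2 | 1.003 | 0.048 |
| 0.5 | 1.018 | 0.040 |
| 0.8 | 1.038 | 0.045 |

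The Monte Carlo standard error of a 5% rejection rate is √(0.05 × 0.95/2000) = 0.005. The rates are therefore at or a little below nominal, with no sign of inflation. Mean estimates were within 0.003 SD of zero with and without the strata.

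**Why the ratios stay small.** Take the 0.8 SD setting. The two factors have variance 2 × (0.8/2)² = 0.32. Given the baseline outcome, 0.32/1.32 = 0.242 of this remains, and it enters follow-up with weight 1 − 0.5, contributing 0.25 × 0.242 = 0.061. Against an error variance of 1 − 0.5² = 0.75, R² = 0.061/0.811 = 0.075, and 1/√(1 − 0.075) = 1.040, in line with the simulated 1.038. Even large stratum differences shrink to a modest R² once the baseline value is adjusted for.

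**The case against.** **A condensed article.** A full analysis plan could add the stratum terms, and the article does not say that the baseline outcome is the only covariate. This stands as a caveat. But the article is not silent on adjustment: it names a covariate, and what it names does not match its own randomisation.

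**The gain may be negligible.** Baseline sway or joint position error already carries much of what age predicts, and the baseline dizziness score nearly determines the dizziness stratum. This stands, and it is why the low end of the range is the more plausible. Nothing in the article supports an R² of 0.20. A reader might infer that age must matter because the tandem-stand entry test changes from eyes closed to eyes open at 45. That is a screening test. The sway outcome is measured under the same conditions at all ages, and the article does not say whether age predicts change in sway given baseline sway.

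**Dizziness.** A reader might infer that the missing adjustment dilutes the result for the hypothesis that specific training "will be superior for reducing dizziness intensity and increasing gait speed". It does not. Dizziness is not an entry criterion, so participants with none have no room to improve, but that depends on who is analysed. With an assumed 10 mm benefit in dizzy participants only (about 9 mm after the scale floor) and 30%, 50% or 70% of participants dizzy, the simulated estimates were 2.6, 4.5 and 6.3 mm both with and without the strata. Standard errors were 1.30, 1.69 and 1.99 mm with them and 1.31, 1.69 and 1.99 mm without. Restricting the analysis to dizzy participants would change the estimand under a planned intention-to-treat analysis. In simulation it gained almost no power (55%, 77% and 89%, against 54%, 76% and 90% in all participants). That choice is debatable and is not part of this point.

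**Therapist.** A reader might also want therapist in the model. Therapist is not a stratification factor: "The physiotherapists will be randomly assigned to each participant using computerized random numbers", and each therapist delivers every arm. Its inclusion is an analyst's option, not a mismatch with the design.

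**Conclusion.** The point holds as a minor one. The stated adjustment set omits the two factors by which the trial randomises. The treatment estimates remain unbiased and the type I error is not inflated. Reported intervals are wider than necessary by about 0.5% to 5% for an assumed residual R² of 0.01 to 0.10. The direction follows from the design. The size rests on that assumption, since the article gives no R², and on 140 analysed participants. The documents do not support reading this as a threat to validity or as a large loss of power.

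**What to change.** In the statistical analysis section, state that the between-group comparisons for all primary and secondary outcomes include age stratum (≤ 45 or > 45 years) and dizziness stratum (yes or no) as fixed main effects, together with the baseline value of the outcome and the two treatment factors. Use the strata as recorded at randomisation, and fix the wording before any unblinded outcome data are seen.

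The cost is one sentence and two degrees of freedom. No new data, extra participants or change to the analysis population is needed.

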### Blinding

The baseline and follow-up assessments will be performed by an independent assessor who is blinded to treatment allocation. The physiotherapists providing the intervention will not be blinded to treatment but will be blinded to outcome assessments throughout the trial.

### Anticipated dates of trial commencement and completion

Recruitment and training of the physiotherapists was undertaken in May 2017 and recruitment of participants has commenced. All participants are expected to have completed the study by end 2019.

### Sample size

The sample size estimates are calculated based on the primary outcomes (postural stability and cervical JPE) from baseline to follow-ups. According to our previous data, we consider a sample size that gives 80% power with a 5% confidence level to detect a significant difference of 21.9 cm^2^ (SD = 12.3) for postural sway and 4.5° (SD = 3.2) for JPE. Sample size estimates were performed using both two-way ANOVA and repeated measure ANOVA (two-tailed) and the optimum number of 35 participants per group is required. To allow for 20% drop out rate, a total sample size of 168 participants (42 per group) will be recruited for this trial.

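### The printed sample-size inputs need about 4 to 17 participants per group, depending on the contrast, so 35 per group at 80% power cannot be reproduced from them

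*Protocol article*

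**What the plan says.** The Sample size section bases the calculation on the two primary outcomes and on the group's own earlier data. It specifies "80% power with a 5% confidence level". The targets are set out in the same sentence, where the trial is sized so that it can "detect a significant difference of 21.9 cm^2^ (SD = 12.3) for postural sway and 4.5° (SD = 3.2) for JPE". The method is given as "two-way ANOVA and repeated measure ANOVA (two-tailed"), and the result is that "the optimum number of 35 participants per group is required". A 20% drop-out allowance takes this to 42 per group and 168 in total.

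The phrase about a confidence level can only mean a 5% significance level, since the Statistical analysis section says "The significance level will be set at 0.05". No split of that level across outcomes or contrasts is stated.

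The section does not name the contrast powered (arm against arm, factorial main effect, or interaction). It does not say whether each SD belongs to a single visit or to a change from baseline, and it gives no within-person correlation. No other detectable effect appears in the article.

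Under Participants, the screening test for JPE uses the same number as the JPE target: "An average absolute error of > 4.5° in any direction is indicative of a deficit in cervical joint position sense".

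**The concern.** Dividing each difference by its SD gives 1.78 for sway and 1.41 for JPE. The protocol's own scale calls 0.8 large. Effects of this size need few participants, so a requirement of 35 per group at 80% power looks inconsistent with the figures beside it.

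This is the article's only power statement. If 35 does not come from the printed inputs, a reader cannot tell what effect the trial was sized to detect. Nor can the reader tell whether the differences, the SDs or the sample size is the misprinted item. The match between 4.5° as a target and 4.5° as a deficit threshold adds to the doubt, because a threshold or a group mean from the earlier data could have been entered as a between-group difference.

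**Working it through.** **Inputs (Sample size section).** Two-sided α = 0.05; power 80%; sway Δ = 21.9 cm², SD = 12.3; JPE Δ = 4.5°, SD = 3.2; stated n = 35 per group. Randomisation is 1:1:1:1 in a 2 × 2 factorial.

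**Standardised differences.** d = Δ/SD: 21.9/12.3 = 1.78; 4.5/3.2 = 1.41.

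**Formula.** A contrast estimated with n per cell has variance k·SD²/n, with k = 1 for a factorial main effect, k = 2 for a pairwise comparison and k = 4 for the interaction. The normal approximation is n = k·(1.96 + 0.8416)²/d² = k·7.85/d². For a pairwise comparison this gives 2 × 7.85/1.78² ≈ 5.0 for sway and 2 × 7.85/1.41² ≈ 7.9 for JPE. The exact version uses the noncentral t distribution with 4n − 4 error degrees of freedom.

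**Attempt to reproduce 35 (exact version, smallest n reaching 80%).**

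| Contrast | Sway | JPE |
|---|---|---|
| Main effect, per cell | 4 | 5 |
| Pairwise, per group | 6 | 9 |
| Four-group omnibus F, per group | 8 | 13 |
| Interaction, per cell | 11 | 17 |
| Pairwise, α/6 | 9 | 14 |
| Interaction, α/6 | 17 | 26 |

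A separate two-group t test gives 7 and 10 for the pairwise case. The choice of formula moves the counts by one or two. Averaging over repeated visits or adjusting for baseline, as the Statistical analysis section plans, does not raise n and usually lowers it. None of these gives 35.

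**Power with 35 per group for the stated differences.** Pairwise and main effects: above 99.9% for both outcomes. Interaction: 99.9% for sway and 98.5% for JPE.

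**What would make 35 right.** For a pairwise contrast at 80% power, SD = Δ/(2.80 × √(2/35)) = Δ/0.670. That is about 32.7 cm² and 6.7°, or roughly 2.7 and 2.1 times the printed SDs.

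**Effect detectable at 80% power, if 12.3 and 3.2 are the SDs of the analysed outcome.** The allowance is 35 × 1.2 = 42, but losing 20% of 42 leaves 42 × 0.8 = 33.6, so a range of 33 to 35 evaluable per group is used. Detectable Δ ≈ 2.80 × SD × √(k/n), with small differences between the approximate and exact versions:

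| Contrast | Sway | JPE |
|---|---|---|
| Main effect | 5.8–6.0 cm² | 1.5–1.6° |
| Pairwise | 8.2–8.6 cm² | 2.1–2.2° |
| Interaction | 11.6–12.1 cm² | 3.0–3.1° |

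**The case against.** The strongest defence is that the section omits details that could change the answer. It refers to change from baseline and to a repeated-measures ANOVA, its source data are not shown, and an article condenses a fuller document. Suppose 3.2° is a single-visit SD, baseline and follow-up are uncorrelated, and the interaction on change scores was powered. The SD then becomes 3.2 × √2 = 4.53° and JPE needs 33 per cell. That is near 35 but not equal to it. The same reading gives only 21 for sway. Zero correlation also sits badly with the test-retest ICC of 0.73–0.84 quoted for JPE, and at a correlation of 0.5 the count drops back to 17. Halving the JPE difference in a pairwise test also gives 33, but contradicts the stated 4.5°. What stands is that 35 cannot be traced from the inputs as printed. It would go too far to say that no conceivable set of unstated assumptions yields it.

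The second defence is that the discrepancy runs in the safe direction, and this stands on the printed inputs. A reader might infer from a faulty calculation that the trial is underpowered. The documents do not support that: for the stated differences and SDs, 35 per group is more than enough.

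A reader might also infer that 4.5° is an impossible target, because someone who enters just above the cut-off would need almost perfect repositioning to gain that much. The cut-off is a floor for entry, not a baseline mean. No baseline mean is given, and participants well above the floor could improve by 4.5°. The coincidence justifies a query only. Nor does anything say that a null result would be judged against 4.5° or 21.9 cm²; the Statistical analysis section interprets effect sizes on the 0.2/0.5/0.8 scale.

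**Conclusion.** The point holds as an error in a stated figure. The difference, SD, level, sidedness, power and result are all printed, and the result does not follow from the rest: 4 to 17 per group across the main-effect, pairwise and interaction contrasts, against 35. The conclusion rests on taking 12.3 and 3.2 as the SDs of the quantity compared and 21.9 cm² and 4.5° as between-group differences, which is how the section presents them.

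The consequence depends on which item is wrong. If the inputs are correct, the trial is larger than they require, its power for them is 98.5% or more rather than 80%, and the effects it can detect at 80% power are much smaller than those stated (about 6 cm² and 1.5° for main effects). If an SD or a difference is mislabelled, the real power cannot be worked out from the article. In either case the justification for 35 needs restating. The validity of the randomisation and analysis is not affected.

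**What to change.** Rewrite the sample-size paragraph and leave enrolment as it is. It should:

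- name the contrast that was powered (main effect, pairwise or interaction);
- say what each SD describes (single visit or change from baseline) and give the correlation used;
- confirm whether 21.9 cm² and 4.5° are between-group differences, and correct or relabel them if they are means or thresholds from the earlier data;
- replace the reference to a 5% confidence level with a two-sided 5% significance level;
- state the effect detectable at 80% power for the number expected to be evaluable.

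The detectable effects tabulated above can be printed only once it is confirmed that 12.3 and 3.2 are the SDs of the analysed outcome. Otherwise they should be recomputed from the right SDs.

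The cost is one paragraph of rewording and a look back at the earlier data.

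### Recruiting 42 per group leaves 33.6, not the required 35, after the stated 20% drop-out; 168 participants cover a loss of only about 16.7%

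*Protocol article*

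**What the plan says.** The Sample size section aims for 80% power at the 5% level ("we consider a sample size that gives 80% power with a 5% confidence level") and reports that "the optimum number of 35 participants per group is required". Its source is described only in general terms: "Sample size estimates were performed using both two-way ANOVA and repeated measure ANOVA (two-tailed"), for printed differences of "21.9 cm^2^ (SD = 12.3) for postural sway and 4.5° (SD = 3.2) for JPE". The next sentence gives the recruitment target: "To allow for 20% drop out rate, a total sample size of 168 participants (42 per group) will be recruited for this trial".

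The section on randomization and allocation concealment fixes equal groups ("with allocation ratio 1:1:1:1"), so 35 per group means 140 in total and 42 per group means 168. The abstract and the Participants section repeat the total of 168. No other drop-out rate or inflation rule appears in the article.

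**The concern.** The two sentences are naturally read together: 35 per group are needed for analysis, 20% of recruits may be lost, and 42 are recruited so that 35 remain. On that reading the arithmetic fails, because a drop-out rate applies to the number recruited and not to the number required.

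At stake is the consistency of the sample-size statement. Follow-up runs to 12 months, so attrition near 20% is a case the protocol itself plans for. If it occurred, the final report would show fewer evaluable participants than the number called required, even though drop-out went exactly as planned. A reader would also take 80% power to hold at 20% loss, and the printed figures do not show that.

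**Working it through.** **Inputs, all from the Sample size section unless noted**
- Required per group: 35, so 4 × 35 = 140 in total (1:1:1:1 allocation, from the randomization section).
- Drop-out rate: 20%.
- Recruited per group: 42, so 4 × 42 = 168.
- Power 80%, 5% level, two-tailed.

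**Step 1. Reproduce the printed target.**
- n × (1 + d) = 35 × 1.20 = 42.0 per group, and 4 × 42 = 168. This matches exactly.

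**Step 2. Apply the stated drop-out to the printed target.**
- Per group: 42 × (1 − 0.20) = 33.6, which is 1.4 short of 35.
- Total: 168 × 0.80 = 134.4, which is 5.6 short of 140.

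**Step 3. Find the target that would leave 35.**
- n / (1 − d) = 35 / 0.80 = 43.75, so 44 per group and 4 × 44 = 176 in total. If only the total is rounded, 140 / 0.80 = 175.
- The printed total is 7 to 8 below this, about 4%, which is more than rounding.

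**Step 4. Find the drop-out rate that 168 supports.**
- 1 − 35/42 = 7/42 = 16.7%.

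**Step 5. Size the consequence, assuming that 35 per group gives exactly 80% power.** The article does not state this assumption in a form that can be checked.
- Normal approximation, two-sided 5%: the standardised effect behind 80% power is 1.960 + 0.842 = 2.802. At 33.6 per group it becomes 2.802 × √(33.6/35) = 2.745, and power is Φ(2.745 − 1.960) = 78.4%.
- Noncentral t, two groups: 77.6% at 33 per group, 78.3% at 33.6 and 78.8% at 34.
- Four-group one-way ANOVA: 78.1% at 33.6 per group.
- Factorial main effect (two arms pooled against two), difference detectable with 80% power by noncentral t: 0.477 SD at 70 against 70 (140 evaluable), and 0.488 SD at 67 against 67 (134 evaluable). That is an increase of about 2%. Neither value is printed in the protocol.

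**Step 6. Check the assumption in step 5 against the printed differences.**
- Read as simple two-group targets, they are 21.9/12.3 = 1.78 SD for sway and 4.5/3.2 = 1.41 SD for joint position error.
- A two-sample t-test would then need about 7 and 10 per group, and power at 33 per group exceeds 99.9% for both.
- So 35 is not reproduced from the printed differences on this reading. The effect metric, within-person correlation and tested term behind the ANOVA calculations are not given.

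**The case against.** The strongest objection concerns the power, not the arithmetic. A reader might infer that the trial fails to deliver its stated 80% power at its own drop-out rate. The document does not support that as a fact. It calls 35 the optimum from two ANOVA calculations whose settings are not shown, and it does not show that 35 is the smallest number reaching 80%. If the printed differences are taken as two-group targets, the slip costs practically no power. This stands, and it makes the 78% conditional. It does not remove the mismatch, because the protocol adopted 35 as its requirement and a reader cannot assume hidden slack in it.

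A second objection is that drop-outs are not wholly lost. The analysis is by intention to treat, multiple imputation is planned as a sensitivity analysis, and there are four post-baseline assessments, so someone lost at 12 months can still inform earlier comparisons. This also stands in part: 134 evaluable is the worst case at any one time point. But imputation does not fully restore lost information, and the sponsor itself chose to inflate for drop-out, so the inflation should match the stated rate.

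Third, a reader might take the multiplication by 1.2 as established. No formula is printed, so the cause is an inference, though the match is exact. The mismatch holds whatever the cause.

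Finally, a reader might conclude that recruitment must rise to 176. Recruitment has begun, the shortfall is small, and correcting the statement is enough.

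**Conclusion.** The point holds as an error in the printed figures: 35 per group required, 20% drop-out and 42 per group recruited cannot all be true. The size is 33.6 against 35 per group, about 134 against 140 in total, with 168 covering a 16.7% loss. This part rests only on applying the drop-out rate to the number recruited.

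The effect on power is at most modest and is conditional. If 35 is the exact number for 80% power and every drop-out is lost to the comparison, power at the planned drop-out is about 78%, and the detectable main effect is about 2% larger. If 35 contains slack, the loss is smaller and could be negligible. Minor: a correction of the statement, with no change to design, recruitment or analysis.

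**What to change.** Keep 168 and correct the sentence in one of two ways:
- State that 168 participants (42 per group) allow for about 16.7% drop-out with 35 per group evaluable.
- Keep the 20% rate and state that it leaves about 33 to 34 per group, with the power or detectable difference at that number taken from the calculation that produced 35.

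The second is more informative if 20% is the sponsor's real expectation over 12 months. The cost is one sentence and a slightly less favourable figure. No further participants are needed for this correction.
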